## Abstract

**Introduction:**

Fertility patients increasingly use web-based and mobile-based apps to access psychosocial care. These digital tools may be a helpful alternative to traditional psychological interventions. Developing and evaluating patient-centred e-mental health tools rooted in evidence-based interventions is a priority. The KindMap is a stand-alone, cost-free e-mental health intervention derived from adapting the Mindfulness Based Programme for Infertility (MBPI) contents to a digital format. The KindMap integrates mindfulness and self-compassion skills training and Acceptance and Commitment Therapy components. This protocol is intended to evaluate the KindMap’s feasibility and explore the extent to which the web-app mode of delivery limited efficacy results are similar to the MBPI in-person format results. Furthermore, it will test the causal theory underlying KindMap.

**Methods and analysis:**

A two-arm 2:1 non-blinded feasibility randomised controlled trial (RCT) will be conducted. Participants are people dealing with infertility, who are able to access the Internet and understand Portuguese or English. Consent participants will complete an online survey at 3-time assessment moments. After baseline assessment, participants will be randomised into the KindMap experimental group (KindMap-EG; with immediate access to the web app) or the waiting-list control group. The primary outcome is well-being (WHO Index-5); secondary outcomes are infertility-related stress (Fertility Problem Inventory—Short Form), anxiety and depression (Patient Health Questionnaire for Depression and Anxiety-4); mindfulness (Five Facet Mindfulness Questionnaire—Short Form), self-compassion (Self-Compassion Scale—Short Form), psychological flexibility (Psy-Flex) and infertility-related self-efficacy are the potential mechanisms of change. KindMap-EG will also complete a feasibility survey.

**Ethics and dissemination:**

The study was approved by the Ethics Committee of the Faculty of Psychology and Educational Sciences of the University of Coimbra (Identifier: CEDI/FPCEUC:78/R_10). The KindMap study may contribute to the existing research on e-health technologies applied to mental health. The study outcomes will be disseminated through publications in peer-reviewed journals and national and international conference presentations.

**Trial registration number:**

NCT05899374.

STRENGTHS AND LIMITATIONS OF THIS STUDYThe KindMap is a web app developed as a stand-alone, cost-free e-mental health intervention that entails a conceptual replication of a previously tested Mindfulness Based Programme for Infertility.The study is a two-arm, parallel-group, non-blinded feasibility study with 2:1 computer-generated randomised allocation to the KindMap experimental group or waiting-list control group.The study has a longitudinal design and addresses the following feasibility dimensions: demand, adaptation, acceptability, implementation, practicality, integration and limited efficacy.Being a feasibility study, the small sample size will not allow for determining the intervention’s efficacy, but will inform the design of a future suitably powered randomised controlled trial.

## Introduction

 Infertility is a clinical condition defined as a reproductive system dysfunction related to the inability to achieve a natural pregnancy after 12 months or more of regular and unprotected sexual intercourse.^1^ The WHO estimates that 8%–12% of reproductive-aged couples worldwide are affected by this condition.^2^ The emotional and psychological impact of infertility is well documented, encompassing profound emotional, relational and social consequences that can lead to long-term mental health impairments.^3 4^ People facing an infertility diagnosis who are pursuing medical treatment tend to face additional burdens due to self-injections, medical examinations, oocyte retrieval, embryo transfer and the (potential) experience of failed treatment cycles. This journey can trigger stress, anxiety and depressive symptoms,^5^,^8^ as well as maladaptive coping mechanisms (eg, experiential avoidance and self-judgement),^9 10^ ultimately diminishing overall quality of life.^11^

Psychological interventions directed at people with infertility have proven effective in improving mental health outcomes.^12^,^16^ Cognitive-behavioural therapies tailored to individuals dealing with infertility have been shown to enhance emotion regulation skills and alleviate psychopathological distress, enhancing well-being.^17^,^22^ One of these interventions designed for people with infertility is the Mindfulness Based Programme for Infertility (MBPI).^19^ The MBPI is an in-person group intervention comprising psychoeducation, mindfulness, compassion and Acceptance and Commitment Therapy (ACT) components. The MBPI was an effective intervention, with results showing a significant decrease in psychopathological symptoms and a significant improvement in emotion regulation processes (eg, mindfulness skills and self-efficacy to deal with infertility) compared with the control group.^19^ Furthermore, participants in the MBPI group continued to reveal therapeutic benefits at a 6-month follow-up and experienced lasting results for up to 7 years.^23^

Fertility patients increasingly use web-based and mobile-based apps to access psychosocial care because these overcome identified barriers, such as financial constraints, travel, scheduling issues, apprehension, fear of being denied/excluded from treatment and stigmatisation.^24 25^ These e-mental health tools are becoming widespread and may be, to some extent, a helpful alternative to traditional psychological interventions, aligning with patients’ needs and preferences.^26^

Therefore, developing and evaluating patient-focused e-mental health tools rooted in evidence-based interventions should be a priority.^3^ Although several support apps have been developed,^27 28^ very few have been evaluated and almost none using high-quality randomised controlled trials (RCTs).^27 29 30^ An exception was MyJourney, a self-guided psychosocial intervention targeting a somehow different group, people who did not fulfil their wish for a child. The MyJourney app has shown to be feasible, revealing high demand, good acceptability and adaptation, and preliminary evidence of efficacy.^31^

In this context, a web app, KindMap, was developed as a stand-alone, cost-free e-mental health intervention derived from adapting MBPI contents to a digital format. The KindMap integrates mindfulness and self-compassion skills training and ACT components. Mindfulness-based programmes, including self-compassion components, are effective in reducing psychopathological distress and have shown a ‘trans-diagnostic effect’ across different clinical conditions, being a highly recommended approach for people coping with infertility.^20^ ACT has also been related to better mental health outcomes in individuals dealing with health conditions (Gloster *et al*, for a review of meta-analyses).^32^ However, studies focusing on ACT within the infertility field are still limited.^33^ Since infertility is a significant life stressor, ACT emerges as a potentially suitable approach that could yield positive and protective effects among individuals experiencing infertility. ACT may contribute to improving mental health indicators, such as anxiety, depression, stress and quality of life, through its targeted components. Furthermore, a systematic review and meta-analysis conducted by Klimczak *et al* also found that ACT could be effectively delivered as a self-guided online intervention.^34^ To our knowledge, none of the developed support apps targeting people with infertility integrates ACT components.^27 29 31^ KindMap will be the first e-mental health integrating mindfulness, self-compassion and ACT components specifically designed for people dealing with infertility.

### Objectives

The current study was designed to evaluate KindMap’s feasibility, specifically feasibility dimensions, such as demand, adaptation, acceptability, implementation, practicality, integration and limited efficacy.^35^ Feasibility results will allow answering to whether the online stand-alone format will be as acceptable as its in-person format and whether one can expect preliminary efficacy of the therapeutic activities incorporated in the intervention. Moreover, it will be possible to assess the extent to which people will sustain their engagement with the tool.

Results will be reported according to the Consolidated Standards of Reporting Trials guidelines for feasibility and pilot studies^36^ and will enlighten needed improvements and adjustments to be performed in the KindMap app and study protocol. If feasible, this study will help define methodological aspects to proceed to the KindMap efficacy study through a large RCT.

## Methods and analysis

### Study design

A two-arm, parallel-group, non-blinded feasibility study with 2:1 computer-generated randomised allocation (www.random.org) to the KindMap experimental group (KindMap-EG; prompt access to KindMap web app) or waiting-list control group (WL-CG; access to KindMap after 10 weeks). The study will encompass three assessment moments: baseline (T1; pre-intervention), 8–10 weeks after baseline (T2; post-intervention) and 10 weeks after post-intervention (T3; only for KindMap-EG). Although there is a recommendation for completing a module per week (similar to the MBPI sessions), the KindMap may be used at the participant’s own pace. Therefore, T2 will occur considering a 2-week flexible period. A T3 assessment will also be implemented at a 10-week interval.

### Participants and recruitment

Recruitment will take place between June and December 2024. An informative email and social media accounts containing information about the KindMap study were created and will be disseminated through the Portuguese Fertility Association (APFertilidade; Patients’ Association) and Fertility Europe (an umbrella organisation of European patients’ associations involved with infertility issues). Interested people will be guided to the KindMap’s landing page, where they can sign up to participate in the study.

Inclusion criteria: (a) presenting self-reporting an infertility diagnosis, (b) age between 18 and 45, (c) being at any stage of the fertility journey (eg, waiting for test results, actively involved in medical treatment, on a wait-list for treatment, having completed one or more treatment cycles), (d) having Internet access and (e) understanding Portuguese or English. Exclusion criteria: (a) currently undergoing any form of psychological intervention, (b) being pregnant and (c) being unable to use the KindMap due to other health difficulties (eg, hearing or visual impairments), all self-reported.

### Procedures

On registering on the KindMap landing page, participants will be asked to complete a questionnaire addressing the eligibility criteria. Participants who meet the eligibility criteria will receive an email containing detailed information about the study and a link to an online platform where they will be asked to provide informed consent (using several mandatory checkboxes) and then proceed to complete the T1 assessment. After T1, consenting participants will be randomly allocated to the KindMap-EG or WL-CG. KindMap-EG participants will have immediate access to the KindMap web app; 8–10 weeks after the baseline, all participants will be invited to complete the T2 assessment by email. At this moment, participants in the WL-CG will be given access to the KindMap web app. 10 weeks later (T3), participants in the KindMap-EG will be invited to complete the T3 assessment. Participants not completing assessments (T1, T2 or T3) will receive reminder emails on days 3, 6 and 9. After receiving the reminders, participants who have not completed the assessment will receive a brief exit questionnaire inquiring about the reasons for withdrawal. The assessment protocols will be hosted on Limesurvey.

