#### Feasibility outcomes

Aligned with Bowen *et al*,^35^ the current study uses several feasibility dimensions to evaluate the KindMap intervention and study protocol. For the KindMap intervention, demand, adaptation, acceptability, implementation, practicality, integration and limited efficacy dimensions will be assessed.

Demand will be assessed by programme adherence (eg, number of users and percentage of modules completed). Adaptation will be assessed by the differences in the hours spent and total number of visits of participants engaging with the KindMap in Portuguese and English. Acceptability will be assessed by user-reported programme satisfaction, perceived usefulness of each module and meditation practices and willingness to recommend the KindMap to peers. Implementation will be assessed by responses to open-ended questions regarding technical problems, the suitability of the 8-week recommended engagement period and barriers and facilitators of use. Practicality will be assessed by the number of participants who use the KindMap as intended (complete eight modules), complete six out of eight modules during the 8–10-week recommended engagement period, and the time taken to use the web app as intended. Integration will be assessed by participants’ perception of using the KindMap skills in everyday life and their willingness to continue doing so. Limited efficacy will be assessed by the effect size estimations of primary and secondary self-reported outcomes changes in the EG-KindMap versus WL-CG. More specifically, Modified Intention-to-Treat (mITT, all participants randomised) and Per-Protocol (PP, only participants who received a sufficient dose) analyses on primary (well-being) and secondary outcomes (infertility-related stress, depression and anxiety) measured at T1, T2 and T3 will be performed.

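### Waiting-list controls get the app with the T2 invitation while T2 answers are still being sought, so some control T2 scores can follow app exposure; Procedures and Study design also give different access times

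*Protocol article*

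**What the plan says.** Four statements in the protocol article bear on this.

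- **T2 invitation (Procedures):** "8–10 weeks after the baseline, all participants will be invited to complete the T2 assessment by email".
- **Control access (Procedures, the next sentence):** "At this moment, participants in the WL-CG will be given access to the KindMap web app".
- **T2 follow-up (Procedures):** "Participants not completing assessments (T1, T2 or T3) will receive reminder emails on days 3, 6 and 9". Only then comes the next step: "After receiving the reminders, participants who have not completed the assessment will receive a brief exit questionnaire". No closing date for T2 is given.
- **Control access (Study design):** the comparator is the "waiting-list control group (WL-CG; access to KindMap after 10 weeks". The same section says of T2: "Therefore, T2 will occur considering a 2-week flexible period".

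Two further statements show what T2 is used for. Under Feasibility outcomes: "Limited efficacy will be assessed by the effect size estimations of primary and secondary self-reported outcomes changes in the EG-KindMap versus WL-CG". Under Study design, the last assessment comes "10 weeks after post-intervention (T3; only for KindMap-EG". T2 is therefore the only assessment after baseline at which the two arms can be compared.

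**The concern.** A waiting-list comparison needs the controls' outcome to be measured before they receive the intervention. Taken in sequence, the Procedures text sends the T2 email, opens the app to controls, and then spends at least nine more days reminding those who have not yet answered. A control who answers after a reminder may already have used the app. The app is self-paced, and the Intervention section says that finishing a module unlocks the next; it mentions no weekly lock.

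The Data analysis plan takes into the modified intention-to-treat set everyone who completes T1 and T2, without requiring that a control's T2 precede app use. The Discussion expects no change in the controls. If the app works, exposed controls move in the same direction as the experimental arm and the estimated difference shrinks. The study is meant to inform a later efficacy trial, so a diluted estimate could carry into that trial's planning. An analysis can identify late answers, but it cannot recover the unexposed score that was never collected.

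**Working it through.** **1. Access as Procedures has it (with the invitation).** A control who answers on the day of a reminder has had the app for 3, 6 or 9 days, and longer if the answer comes later. At the recommended one module per week, 9 ÷ 7 = 1.3 of 8 modules. A control who answers at once has had almost no exposure.

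**2. Access as Study design has it (after 10 weeks = day 70).**

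- Invitation at week 8 (day 56): the last reminder falls on day 56 + 9 = 65, which is 70 − 65 = 5 days before access. There is no overlap up to that reminder.
- The last reminder reaches day 70 when the invitation goes out on day 70 − 9 = 61, or 61 ÷ 7 = 8.7 weeks.
- Invitation at week 10 (day 70): the two sections coincide, and the whole nine-day reminder period follows access.

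The two sections agree only in the last case. The Study design timing removes the overlap for early invitations but not for those from about week 8.7 onward.

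**3. Scale, by assumption only.** The documents give neither the share of controls who answer after using the app (q) nor the fraction of the full effect they would carry by then (g). If both were known, the contrast would be multiplied by 1 − q × g.

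The nearest figure in the plan is the sample size of 54 (f = 0.25, alpha 0.05, power 0.95, two groups, two time points). With λ = f² × N × 2 ÷ (1 − ρ), 1 and N − 2 degrees of freedom, and ρ = 0.5 assumed because none is stated, λ = 0.0625 × 54 × 2 ÷ 0.5 = 13.5 and power is 0.950. The plan's figure is reproduced for equal arms. With 2:1 allocation λ is multiplied by 4 × (2/3) × (1/3) = 0.889, and power is 0.925. Replacing f by f × (1 − q × g) gives:

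| q (assumed) | g (assumed) | contrast × | power, equal arms | power, 2:1 |
|---|---|---|---|---|
| 0 | – | 1 | 0.950 | 0.925 |
| 0.10 | 0.125 | 0.988 | 0.945 | 0.919 |
| 0.25 | 0.25 | 0.938 | 0.922 | 0.890 |
| 0.50 | 0.25 | 0.875 | 0.884 | 0.845 |
| 0.50 | 0.50 | 0.750 | 0.772 | 0.722 |

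If benefit were proportional to modules completed, g = 0.125 would be one module of eight, 0.25 two and 0.50 four. Four modules in about nine days is far quicker than the recommended pace. The table shows how the dilution behaves; it does not estimate what will happen.

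**The case against.** **The wording may be loose.** The article uses the word moment for its assessment stages, so the access sentence could mean the T2 stage or T2 completion rather than the sending of the email. Figure 1, the participant flowchart, is not shown and may settle the order. This stands as a caution. Even so, the sentence follows directly on the invitation, nothing ties access to submission, and Study design gives a different time. The text needs reconciling on either reading.

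**Study design may already protect the comparison.** It does so in part, for invitations before about week 8.7.

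**This is an exploratory estimate.** The article says that the small sample will not allow efficacy to be determined, and limited efficacy is one of seven feasibility dimensions. That stands, and it limits the severity.

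**The analysis plan may deal with late answers.** It may, and the app already has to record use for the feasibility outcomes. The access trigger, however, is something the article states, not a detail it leaves open.

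A reader might go further in two directions that the documents do not support:

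- *T2 timing differs by arm.* The two-week flexibility is explained by app pace, which only the experimental arm has during that period. But all participants are invited at 8–10 weeks, and nothing links an invitation to module progress.
- *Controls lose their reason to complete T2.* Nothing in the article says that controls answer in order to gain access.

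**Conclusion.** The point holds, with moderate severity. Followed as written, Procedures allows control T2 scores to be recorded after several days of app access, in the only controlled comparison the trial has, and it conflicts with Study design on when access opens. The bias is toward zero, provided that early use of the app has some benefit.

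A reader might want to attach a percentage to the loss, or to conclude that the comparison is invalid. Neither is supported. The share of controls exposed before answering and the benefit they would have gained are not in the documents. At the recommended pace exposure is little more than one module, and prompt responders have almost none, so the bias is probably modest. That last judgement is an inference from the timings, not a calculated result.

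**What to change.** 1. Reconcile Study design and Procedures with a single rule: each control's access opens when that participant submits T2 or when the T2 reminder window closes, whichever comes first. State the day on which the window closes.
2. Use the app's usage log and the survey submission date to flag any control T2 response dated after that participant's first login. Keep these responses in the main analysis and add a sensitivity analysis without them. Late responders may differ from prompt ones, so leaving them out should not become the main result.

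The 8–10-week flexibility for T2 can stay as it is. The cost is one procedural sentence, one access trigger and a comparison of dates. The drawback is that some controls wait up to about nine more days for the app.

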### Sample size

G*Power calculations for within-between interaction Analysis of Variance (ANOVA) repeated measures (two-conditions, two-time points), assuming a p=0.05, effect size *f*=0.25, power=0.95, recommend a sample size of 54. Assuming participation and retention rates of 60% and 34% (observed in similar apps), we will recruit n=180 participants. This sample size is in accordance with Sim and Lewis^37^ recommendation of at least 50 participants for feasibility studies.

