### Randomisation

Figure 1 shows the expected flow of participants throughout the study. Consenting participants will be randomised in a 2:1 ratio through computer-generated randomisation after completing the T1 assessment. Randomisation will be guaranteed by a third researcher (different from the two responsible for enrolment and allocation of the participants to the EG-KindMap and WL-CG groups) who will only know the participants’ code. Participants randomised into KindMap-EG will be stratified into a Portuguese or English-speaking group. All participants will be informed of the randomisation results.

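### The 54 quoted for 95% power is the equal-allocation figure; under the trial's 2:1 randomisation it gives 92.5%, and about 61 completers are needed

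*Protocol article*

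**What the plan says.** The Sample size section of the protocol article describes a G*Power calculation for a "within-between interaction Analysis of Variance (ANOVA) repeated measures (two-conditions, two-time points"), "assuming a p=0.05", "effect size *f*=0.25" and "power=0.95, recommend a sample size of 54". It gives no allocation ratio and no correlation between the two time points. It then inflates to a recruitment target of 180: "Assuming participation and retention rates of 60% and 34% (observed in similar apps"). It adds that the size meets a published recommendation of at least 50 participants for feasibility studies.

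The allocation is unequal everywhere it is mentioned. Study design describes a "non-blinded feasibility study with 2:1 computer-generated randomised allocation", and Randomisation says "Consenting participants will be randomised in a 2:1 ratio". The abstract and the strengths-and-limitations list agree.

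That list also says that "the small sample size will not allow for determining the" intervention's efficacy.

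**The concern.** The repeated-measures interaction calculation in question assumes groups of equal size. For a fixed total, a 2:1 split carries less information about a between-arm difference than a 1:1 split, so a total computed for equal groups cannot deliver the same power at 2:1. If 54 is the equal-group number, the article attaches 95% power to a design it does not use.

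What is at stake is how the limited-efficacy estimates are read and how the later, larger trial is planned. Both lean on the stated power, and the effect it refers to appears only as f=0.25. Without a translation into a difference in change, readers cannot see how large an effect the 95% covers.

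**Working it through.** **Inputs.** From Sample size: alpha 0.05, f = 0.25, power 0.95, N = 54, two groups, m = 2 time points, participation 60%, retention 34%, target 180. From Randomisation: 2:1. Assumed: T1–T2 correlation rho = 0.5 (not stated), and the same retention in both arms.

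**Step 1: reproduce 54.** With equal groups the noncentrality is lambda = f² × N × m / (1 − rho) = 0.0625 × 54 × 2 / 0.5 = 13.5, on 1 and 52 df. Power is 0.9501; N = 53 gives 0.9464. So 54 is exactly the 27:27 result at rho = 0.5. At rho = 0.3 the calculation returns 75 (76 for equal groups), and at rho = 0.7 it returns 34. Of the values tried, only 0.5 gives 54.

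**Step 2: what f = 0.25 means.** In a balanced 2×2 interaction it places a deviation of 0.25 SD in each of the four cells, so the between-arm difference in change is 4 × 0.25 = 1.0 raw-score SD, whatever the correlation. The SD of change is √(2(1 − rho)) raw SDs, which is 1 at rho = 0.5, so there the effect is also 1.0 SD of change. As a check, a two-sample comparison of change scores at 27:27 with d = 1.0 again gives 0.9501.

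**Step 3: same effect at 2:1.** Now lambda = d² × n1 × n2 / (n1 + n2), with d = 1.0 and n1 + n2 − 2 denominator df.

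| Completers | Split | lambda | Power |
|---|---|---|---|
| 54 | 27:27 | 13.5 | 0.950 |
| 54 | 36:18 | 36×18/54 = 12.0 | 0.925 |
| 60 | 40:20 | 40×20/60 = 13.3 | 0.9485 |
| 61 | 41:20 | 41×20/61 = 13.4 | 0.9501 |
| 63 | 42:21 | 42×21/63 = 14.0 | 0.957 |

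The shortfall at 54 is 2.5 percentage points, or 61 − 54 = 7 completers. The difference detectable with 95% power at 36:18 is 1.06 SD.

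**Step 4: smaller effects at 36:18, rho = 0.5.** Power is 0.78 for 0.8 SD and 0.40 for 0.5 SD.

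**Step 5: what 180 yields.**
- Retention only: 180 × 0.34 = 61.2, about 61 completers (41:20), power 0.950.
- Both rates: 180 × 0.60 × 0.34 = 36.7, about 37 completers (25:12), lambda = 25×12/37 = 8.1, power 0.79.

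Neither reading gives 54. Working back from 54, retention alone needs 54/0.34 = 159 people, and both rates need 54/(0.60 × 0.34) = 265.

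**The case against.** The strongest reply is that 180, not 54, is the recruitment target. If 180 people are randomised and 34% are retained, 61 completers are expected, which is what 95% needs at 2:1 (61/0.34 = 179.4). On that reading the allocation loss is absorbed. This stands, and it rules out the stronger inference a reader might draw, that the trial as designed lacks 95% power. The article does not settle the matter, because it names a 60% participation rate alongside retention and does not say which people the 180 counts. Applying both rates gives about 79%.

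Second, the allocation error is small. That also stands. One could add that an f defined with allocation weights would keep 95% power at 36:18 for a 1.06 SD difference, but the named procedure assumes equal groups.

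Third, the missing correlation and the missing support for f=0.25 are omissions that a condensed article may leave to a fuller document. I agree and do not count them as errors. Translating f into 1.0 SD changes no power at the stated f; it only shows what the figure refers to.

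Fourth, a reader might see a contradiction between 95% power and the statement that efficacy cannot be determined, or fear that a null result will be taken as strong evidence of no benefit. The document does not bear out either in full. Feasibility outcomes defines limited efficacy as effect-size estimation, the Data analysis plan calls it exploratory, progression rests on traffic-light criteria for the feasibility outcomes, and the size has a separate feasibility basis of at least 50 participants. The tension is mild.

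**Conclusion.** The statement that 54 gives 95% power is wrong as written for this trial. It is the 27:27 figure; at the 2:1 ratio actually used, 54 completers give 92.5% for the same 1.0 SD difference in change, and 95% needs about 61. These values rest on a correlation of 0.5, which is inferred because it reproduces 54.

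The document does not show that the design's expected power is below 95%. That turns on what 180 counts, and the two readings give about 95% and about 79% (assuming equal retention across arms). This ambiguity moves power more than the allocation slip does.

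Severity is minor: the sample is for a feasibility study, efficacy is treated as exploratory, and the correction changes nothing in the conduct of the trial.

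**What to change.** Recompute for 2:1 and replace the sentence in Sample size with one of these statements, each for a 1.0 SD between-arm difference in T1–T2 change, two-sided alpha 0.05 and correlation 0.5 (the authors should confirm the correlation they entered):
- 54 completers (36:18) give 92.5% power; or
- 61 completers (41:20) give 95% power.

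Add that at 36:18 power is about 40% for a 0.5 SD difference.

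Then state whether 180 counts people randomised (about 61 completers, power about 95%) or people approached or registered (about 37 completers, power about 79%), and report the power that matches.

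The cost is a few sentences. If the second reading is the intended one, the reported power becomes visibly less favourable.

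### The recruitment target of 180 does not follow from 54 analysable participants with 60% participation and 34% retention; those figures require about 265

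*Protocol article*

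**What the plan says.** The Sample size section of the protocol article bases the calculation on the within-between interaction of a repeated-measures ANOVA ("two-conditions, two-time points"), with a significance level of 0.05 and "effect size *f*=0.25". The result is given as "power=0.95, recommend a sample size of 54". The next sentence moves from 54 to the target: "Assuming participation and retention rates of 60% and 34% (observed in similar apps), we will recruit n=180 participants". The intermediate step is not shown. The correlation between time points is not given, and the paragraph does not mention unequal allocation.

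The Randomisation section sets the ratio: "Consenting participants will be randomised in a 2:1 ratio", after the T1 assessment. The Procedures section places the eligibility questionnaire, the study email, consent and T1 before that step. The Data analysis plan defines the modified intention-to-treat set as those who complete T1 and T2. The Feasibility outcomes section defines the same set as everyone randomised.

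**The concern.** The paragraph states a need, two loss rates and a result, and the result cannot be obtained from the other three. The article itself gives the inputs and the output, so this is not a detail left to a fuller document.

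What is at stake depends on the step at which 180 is counted. If it is counted before the 60% participation step, the expected number of completers falls well short of the 54 on which the stated power rests. If it is counted at randomisation, the completers suffice, but the recruitment effort is larger than the text conveys, within a window of June to December 2024. Participation and retention are also feasibility outcomes of this study, judged by progression criteria and meant to inform a later trial. The planning figures for those rates should therefore be consistent.

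**Working it through.** **Inputs from the protocol article.** Sample size section: alpha 0.05, f = 0.25, power 0.95, N = 54 in total, two groups and m = 2 time points, participation 0.60, retention 0.34, target 180. Randomisation section: 2:1. **Assumption, not in the document:** correlation rho = 0.5 between time points.

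**1. Reproduce the 54.** For the interaction test, lambda = f² x N x m/(1 - rho), with 1 and N - 2 degrees of freedom.
- N = 54: lambda = 0.0625 x 54 x 2/0.5 = 13.5; power 95.0%.
- N = 52: power 94.2%.

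So 54 reproduces at rho = 0.5. At rho = 0.3, 54 would give 86.2%, and at rho = 0.7 it would give 99.6%. The plan's own figure therefore points to 0.5.

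**2. Try to reproduce the 180.**

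| Use of the rates | Calculation | Number to recruit |
|---|---|---|
| Both rates | 54/(0.60 x 0.34) = 264.7 | 265 |
| Retention only | 54/0.34 = 158.8 | 159 |
| Participation only | 54/0.60 | 90 |
| Participation, with 34% read as attrition | 54/(0.60 x 0.66) = 136.4 | 137 |
| 34% read as attrition, alone | 54/0.66 = 81.8 | 82 |

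None gives 180. The yield implied by 180 is 54/180 = 30%, for example 60% x 50%. The stated yield is 0.60 x 0.34 = 20.4%.

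**3. If 180 is counted before participation.** 180 x 0.60 = 108 are randomised, and 108 x 0.34 = 36.7, or about 37, complete T2.

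Power at N = 37 on the plan's own calculation: lambda = 0.0625 x 37 x 2/0.5 = 9.25; power 84.1%. With rho = 0.3 it is 70.5%, and with rho = 0.7 it is 96.8%.

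Counting 2:1 allocation with the mean difference held fixed multiplies lambda by 4 x (2/3) x (1/3) = 0.889. Power is then 79.3% at the unrounded 36.72 and 79.6% at 37. On the same basis N = 54 gives 92.5%.

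**4. If 180 means randomised.** 180 x 0.34 = 61.2, or about 61 completers. Power is 97.0%, or 95.2% counting 2:1. Reaching 180 randomised requires inviting 180/0.60 = 300 eligible people.

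**The case against.** The strongest reply is that a recruit is an enrolled person. On that reading only retention applies, 61 people complete, and the requirement of 54 is met with about 95% power even at 2:1. The participant flowchart is not shown and may say at which step 180 is counted. This stands as far as the shortfall goes: a reader might infer that the trial must end with 37 completers, and the document does not establish that. It does not rescue the paragraph. Both rates are offered as the basis for 180, whereas on this reading participation plays no part and retention alone gives 159. Another route, 2 x 54/0.60 = 180, works only if 54 is taken per arm and the 34% is ignored, which the text does not say.

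Other stronger readings are tempting but unsupported:

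- **A fall from 95% to 79%.** This compares two bases. Like for like, the fall is from 95% to 84%, or from 92.5% to about 79% once 2:1 is counted.
- **Effect sizes less precise than stated.** The document states no precision or interval width.
- **The cited recommendation of at least 50 is missed.** The document does not say that this counts completers, and 180 recruited or 108 randomised both exceed it.

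Two further cautions are fair. The 37 follows the Data analysis plan's completer definition; under the definition in the Feasibility outcomes section the set would be the 108 randomised, although about 37 would still have T2 data. The text also does not say whether 34% is retention to T2 or to T3; it is applied here to T2, because the calculation uses two time points.

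**Conclusion.** The target is wrong as written: 54 in total, 60% and 34% require about 265, and 180 does not result from any use of those figures. The consequence is conditional. On the plain reading, 180 counted before participation, about 37 completers are expected, with about 84% power (70% to 97% for correlations of 0.3 to 0.7), or about 79% counting 2:1. If 180 means randomised, the 54 is met and what remains wrong is the stated derivation and the missing figure of about 300 invited. The power figures rest on the unstated correlation of 0.5, and the 2:1 figures also on a fixed mean difference.

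The weight is moderate. The article's own strengths and limitations say that the sample is too small to determine efficacy, and limited efficacy is one of seven feasibility dimensions for the intervention.

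**What to change.** Rewrite the Sample size paragraph so that the step from 54 to the target is shown and the stage at which 180 is counted is named.

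- **If 180 is the number randomised after T1:** say so, and give about 300 eligible people to be invited (180/0.60) and about 61 expected T2 completers (180 x 0.34).
- **If 180 is counted before participation:** restate the expected analysed sample as about 37 and the power for f = 0.25 as about 84% (about 79% with 2:1 allocation) in place of 95%.

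In either case, state the correlation assumed between time points.

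The cost is wording only, provided each statement describes what is already planned; the second makes the stated power less favourable. If 180 was in fact counted before participation, adopting the first would be a real enlargement, from 108 to 180 randomised and from 180 to 300 invited, within the same recruitment window.
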